# Evaluating the use of fibrin glue for sealing low-output enterocutaneous fistulas: study protocol for a randomized controlled trial

**DOI:** 10.1186/s13063-015-0966-9

**Published:** 2015-10-07

**Keywords:** enterocutaneous fistulas, fibrin glue, glue sealing

## Abstract

**Background:**

The management of an enterocutaneous fistula poses a significant challenge to surgeons and is often associated with a costly hospital stay and long-term discomfort. The use of fibrin glue in the fistula tract has been shown to promote closure of low output enterocutaneous fistulas. Our previous nonrandomized study demonstrated that autologous platelet-rich fibrin glue treatment significantly decreased time to fistula closure and promoted closure rates. However, there are several limitations in the study, which may lead to bias in our conclusion. Thus, a multicenter, randomized, controlled clinical trial is required.

**Methods/Design:**

The study is designed as a randomized, open-label, three-arm, multicenter study in nine Chinese academic hospitals for evaluating the efficacy and safety of fibrin glue for sealing low-output fistulas. An established number of 171 fistula patients will undergo prospective random assignment to autologous fibrin glue, commercial porcine fibrin sealants or drainage cessation (1:1:1). The primary endpoint is fistula closure time (defined as the interval between the day of enrollment and day of fistula closure) during the 14-day treatment period.

**Discussion:**

To our knowledge, this is the first study to evaluate the safety and efficacy of both autologous and commercial fibrin glue sealing for patients with low-output volume fistulas.

**Trial registration:**

NCT01828892. Registration date: April 2013.

**Electronic supplementary material:**

The online version of this article (doi:10.1186/s13063-015-0966-9) contains supplementary material, which is available to authorized users.

## Background

An enterocutaneous fistula (ECF) still remains as one of the most complex and challenging complications encountered in surgical practice [1]. Its management often requires a costly hospital stay and multidisciplinary care due to high morbidity and mortality induced by sepsis, hemorrhage, malnutrition and electrolyte disturbances [2, 3]. Staged fistula treatment involves recognition and stabilization, anatomic definitioxn and decision, and definitive operation. With sufficient time, conservative treatment can result in spontaneous fistula closure, with rates varying from 15 % to 71 % [4]. However, this also results in long-term discomfort.

Use of fibrin glue (FG) in the fistula tract has been shown to promote closure of low-output ECFs. As a noninvasive option, it could avoid the risk of developing further dehiscence compared to surgical operations. The application of glue has been reported in recent years for intestinal fistula in case reports [5, 6] and small series [7–10]. Commercial fibrin sealants are usually made from porcine/bovine blood products, whereas autologous adhesives have potential advantages, such as a low risk of infection transmission [11] and provision of a matrix for tissue regeneration [12]. Both are used in clinical practice, but they have not yet been compared to fistula sealing.

Our previous study demonstrated that autologous platelet-rich fibrin glue (PRFG) treatment significantly decreased time the time to fistula closure and promoted closure rates. During the follow-up, no treatment-related adverse events or severe adverse events were observed [13]. The previous study was a prospective, nonrandomized single-center study. There were several limitations in the nonrandomized study, which may have led to bias in our conclusion. Thus, a multicenter, randomized, controlled clinical trial is designed to evaluate the glue application in the treatment of patients with low-output volume ECFs.

### Objectives

The objective of this study was to investigate the efficacy and safety of glue sealing (using PRFG or the commercially available fibrin sealant Yueling™) in the management of patients with low-output ECFs.

### Trial design

The trial is designed as a multicenter, open-label, randomized, controlled trial with three parallel groups (two treatment groups and one control group) and a primary endpoint of fistula closure time during the 14-day treatment period. The randomization will be performed by Internet-based software with a 1:1:1 allocation. No blinding will take place in this study.

## Methods/Design

### Participants, interventions and outcomes

#### Study setting

This is a randomized, open-label, therapeutic trial to investigate glue-sealing therapy, and the trial is being conducted in nine Chinese academic hospitals. The nine study sites are distributed in Jiangsu Province, Jiangxi Province, Shandong Province, Beijing, Henan Province, Neimenggu Region and Jilin Province, which cover most parts of East, North, Northeast and Northwest China. The trial began in March 2014 and is scheduled to be completed by the end of 2017.

#### Eligibility criteria

For inclusion, patients must meet the following criteria:Age ≥18 years.Single tubular ECF.Fistula tract length >2 cm.Low output volume (<200 ml/24 h).Written informed consent.

Subjects presenting with any of the indicated general or indication-specific exclusion criteria will not be included in the trial.

The general exclusion criteria include the following:Subject lacks legal capacity.Subject unable to understand the nature, scope, significance and consequences of this clinical trial.Simultaneously participating in another clinical trial or participated in any clinical trial involving administration of acupuncture within 30 days prior to inclusion.Subject exhibits a physical or psychiatric condition, which at the investigator’s discretion may put the subject at risk, may confound the trial results or may interfere with the subject’s participation in this clinical trial.Known or persistent abuse of medication, drugs or alcohol.Current or planned pregnancy or is nursing.

Indication-specific exclusion criteria include the following:Cancer-infiltrated fistula.Intra-abdominal abscess near the fistulas.Foreign bodies inside the fistula tracts.Distal bowel obstruction.Inflammatory bowel disease.

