#### Interventions

Qualified subjects will randomly be assigned to one of three study groups: two treatment groups offered autologous PRFG (Group A) or commercial porcine fibrin sealants (Group B) and one control group with drainage cessation (Group C).

All groups receive standard of care (SOC) before assessment for inclusion. The SOC comprises supportive measures to stabilize the fistula patient, including fluid/electrolyte balance, bowel rest, nutritional replacement, wound care, and antibacterial therapy in patients with signs of systemic sepsis or inflammation with pain. Nasogastric or nasointestinal feeding will be provided whenever possible; otherwise, parenteral nutrition along with 0.9 g/24 h somatostatin (Stilamin, Serono, Switzerland) will be infused intravenously. To assist in remission of infection, normal saline will be dripped continuously to rinse the fistula tracts; at the same time, percutaneous suction drainage of these tracts is conducted. Nursing staff monitor the daily external output by collecting output volumes. Once the daily fistula volumes decrease to 200 ml, the patients will be evaluated by the coordinating center.

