#### Sample size

The sample size is to be calculated based on detecting the minimal, clinically relevant difference in the success rates of the three arms. Our preliminary study, which enrolled 145 patients, compared the efficacy of PRFG application (PRFG group) with drainage cessation (control group) when low output volume was achieved (<200 ml/d). During the 28-day treatment period, 77 % (58/75) of the patients in the PRFG group experienced fistula closure in comparison to 57 % (40/70) in the control group (*P* = 0.0127) [13]. The unpublished data of the pilot study demonstrated that closure rates were 80 % (60/75) in the PRFG group and 50 % (35/70) in the control group during the 14-day observation period. Due to the above raw data, the closure rates in the two treatment groups and one control group are assumed to be 80 % and 50 %, respectively. In this way, 51 patients per group are needed for this trial based on an alpha of 0.05, with a power of 90 %. Taking into account a drop-out rate of 10 %, a total sample size of 171 patients would be included, with 57 participants in each group.

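### The 30-day look-back names acupuncture trials, which play no part in this study, and so lets in patients who have just finished a glue, sealant or drug trial

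*Protocol article*

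**What the plan says.** In the protocol article, Eligibility criteria, one general exclusion criterion governs participation in other trials: "Simultaneously participating in another clinical trial or participated in any clinical trial involving administration of acupuncture within 30 days prior to inclusion". It has two limbs. The first bars concurrent participation in any other trial. The second is the only look-back on earlier trials, and its period, "within 30 days prior to inclusion", attaches to acupuncture trials alone.

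The Interventions section describes three arms: autologous platelet-rich fibrin glue, a commercial porcine fibrin sealant, and drainage cessation as control. The indication-specific exclusions are "Cancer-infiltrated fistula.Intra-abdominal abscess near the fistulas.Foreign bodies inside the fistula tracts.Distal bowel obstruction.Inflammatory bowel disease". None concerns earlier trial participation. A discretionary exclusion covers a physical or psychiatric condition that, among other things, "may confound the trial results or may interfere with the subject’s participation in this clinical trial".

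Under Outcomes, the primary endpoint is closure time during 14 days from enrolment, and adverse events are counted up to 180 days.

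**The concern.** A look-back on earlier trials keeps the lingering effects of another investigational product out of the outcomes of the present one. Here it is tied to an exposure unrelated to the study and leaves out those that could matter: another glue, another sealant, or a drug under test.

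This is more than an abbreviated list. The article states a specific rule and ties it to the wrong exposure. Sites applying it literally would exclude patients for no reason relevant to this trial and admit others whose closure or adverse events might partly reflect a product received just before enrolment. Sites that guess at the intended meaning would apply different rules across the nine hospitals.

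**Working it through.** **Does acupuncture have a role anywhere?** It is absent from Objectives, Interventions (including standard of care), Outcomes, Statistical analysis and Harms. The eligibility clause is its only appearance.

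**How the rule sorts patients.** The printed clause is set against one covering any interventional trial in the same 30 days:

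| Patient | As printed | Any interventional trial, 30 days |
|---|---|---|
| Still in another trial of any kind | excluded (first limb) | excluded |
| Acupuncture trial ended 3 weeks ago | excluded | excluded |
| Sealant or drug trial ended 3 weeks ago | admitted | excluded |
| Sealant or drug trial ended yesterday | admitted | excluded |
| Any trial ended more than 30 days ago | admitted | admitted |

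The third and fourth rows are the gap.

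**Do other clauses close it?** The first limb does not, because participation has ended. The discretionary clause requires a physical or psychiatric condition, and having completed a trial is neither. The five indication-specific items describe the fistula and the bowel. The foreign-body item might be read to include residual glue, but the article does not say so, and it could not cover a drug.

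**Could an earlier effect reach the outcome windows?** Let participation in the other trial end k days before inclusion. The primary window then runs from day k to day k + 14 after that trial. Assume, for illustration, that the protocol's own 30 days is how long an effect may last. The whole primary window lies inside it when k + 14 ≤ 30, that is k ≤ 16, and part of it does for k = 17 to 29. The 180-day adverse-event period starts inside it for every k below 30.

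**Does any planned figure depend on the clause?** No. The sample size uses closure of 80% against 50%, alpha 0.05 and power 90%. The pooled two-sided formula gives

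n = [1.960·√(2·0.65·0.35) + 1.282·√(0.80·0.20 + 0.50·0.50)]² / 0.30² = (1.322 + 0.821)² / 0.09 ≈ 51.0,

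which is just over 51 and rounds up to 52. The arcsine formula gives 50.7, hence 51. Power at 51 per group is 0.900. With 10% drop-out, 51/0.90 = 56.7, so 57 per group and 3 × 57 = 171. The plan's figures reproduce, and rewording the criterion changes none of their inputs.

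**Size of the effect.** The documents give no share of patients with a recently completed trial, so no bias or dilution can be computed.

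**The case against.** The strongest reply is that this is a drafting slip with little practical weight. Patients in any ongoing trial are already excluded. The documents describe no competing glue, sealant or drug trial at the nine hospitals. Entry requires a fistula that is still draining and has been imaged, and randomisation balances recent trial participants across arms on average. All of this stands and limits the severity. It does not make the rule correct. Nor does the article format excuse it: a fuller protocol may word the criterion differently, but the published rule would then still need correcting.

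A reader might go further and infer that the clause also admits patients whose fistula was sealed in routine care without success, since the Background says of the two glue types: "Both are used in clinical practice, but they have not yet been compared to fistula sealing". The documents do not support building that on this clause. A trial-participation window, however worded, would not cover routine care. A separate criterion on earlier sealing may stand in the full protocol. The stated objective, "efficacy and safety of glue sealing (using PRFG or the commercially available fibrin sealant Yueling™) in the management of patients with low-output ECFs", is not restricted to patients who have never had glue. The Background remark is general and says nothing about these sites. Excluding such patients would be a design preference.

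A reader might also infer a loss of power from earlier glue failures. The plan assumes that "the closure rates in the two treatment groups and one control group are assumed to be 80 % and 50 %, respectively". If a share f of patients had failed glue before and closed at 50% in every arm, the glue rate would be 0.80 − 0.30f. Power with 51 per group would be 0.863, 0.818 and 0.767 at f = 5%, 10% and 15%. The arithmetic is right, but f has no source in the documents, and the model gives these patients no benefit from glue while leaving their control closure undiminished. If they closed at 40% in control instead, f = 15% would give 0.755 against 0.50 − 0.10 × 0.15 = 0.485. The test statistic is then (0.27 − 1.960 × 0.0961)/0.0923 = 0.884, and power is 0.81. The result depends on unsupported inputs and concerns routine-care glue, not the acupuncture wording.

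**Conclusion.** The point holds as an error in one operative eligibility rule. The only look-back on earlier trials screens for an exposure foreign to this study and leaves recently completed glue, sealant or drug trials uncovered. That follows from the text alone. That the wording was carried over from another protocol is plausible, but it is an inference and the point does not need it.

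Severity is minor. The possible harm is carry-over into the 14-day or 180-day outcomes and a less clearly defined population. It depends on such patients presenting and on effects outlasting the other trial, and the documents quantify neither. Systematic bias between arms is not shown, and no numerical loss of power can be attributed to the clause.

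**What to change.** Replace the second limb so that the criterion excludes concurrent participation in another clinical trial, or participation in any interventional clinical trial within 30 days before inclusion. If the full protocol already says this, correct the published description.

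Optionally, add one history item to the case report form recording whether the current fistula was sealed before enrolment, and use it in a sensitivity analysis.

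The cost is a one-sentence change. Under Protocol amendments, a change to the patient population needs a formal amendment with ethics approval, so it is not an administrative correction. A few patients would become ineligible. The sample size is unaffected. The Trial status section reports recruitment as under way, so the change would apply to patients enrolled from then on.

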#### Interventions

Qualified subjects will randomly be assigned to one of three study groups: two treatment groups offered autologous PRFG (Group A) or commercial porcine fibrin sealants (Group B) and one control group with drainage cessation (Group C).

All groups receive standard of care (SOC) before assessment for inclusion. The SOC comprises supportive measures to stabilize the fistula patient, including fluid/electrolyte balance, bowel rest, nutritional replacement, wound care, and antibacterial therapy in patients with signs of systemic sepsis or inflammation with pain. Nasogastric or nasointestinal feeding will be provided whenever possible; otherwise, parenteral nutrition along with 0.9 g/24 h somatostatin (Stilamin, Serono, Switzerland) will be infused intravenously. To assist in remission of infection, normal saline will be dripped continuously to rinse the fistula tracts; at the same time, percutaneous suction drainage of these tracts is conducted. Nursing staff monitor the daily external output by collecting output volumes. Once the daily fistula volumes decrease to 200 ml, the patients will be evaluated by the coordinating center.

For patients in Group A, autologous PRFG is prepared as described previously [14]. The platelet-rich cryoprecipitate and thrombin are obtained from the whole blood of patients in Group A at least 24 h prior to the start point. Blood collecting packs, prepared with anticoagulant (citrate phosphate dextrose), are used for the collection of whole blood (300 to 400 ml). The platelet-rich plasma (PRP) is separated from the blood by centrifugation at 6 min at 1,000 x*g* twice at ambient temperature. The PRP is transferred to a new pack, and the amount will be determined by weight. From 40 g PRP, equally transferred to two new 300 ml empty packs, the euglobulin fraction is precipitated by dilution with 180 ml citric acid (2.84 mM) in each pack. After thorough mixing, the pack is centrifuged at 3,000 x*g* for 5 min at 4 °C. The supernatant is removed and the precipitate dissolves in 1.625 ml CaCl_2_ (0.1 M). The pH is adjusted by the addition of 1.0 ml NaHCO_3_ (75 mM) in order to initiate the activation of the prothrombin to thrombin [15]. The clot formation is terminated after 30 minutes, and the liquid thrombin solution is removed into microcentrifuge tubes. At the same time, the cryoprecipitate is produced from the rest of the plasma, which is frozen at −80 °C for at least 6 h first and then thawed at 4 °C. After centrifugation at 4,000 rpm/min for 8 min, the cryoprecipitate is harvested by removal of the cryoprecipitate-poor plasma. When applied, fibrinogen and thrombin are thawed at 37 °C from −20 °C until recovery of the liquid state.

Patients in Group B receive glue sealing with commercial sealants. The Porcine Fibrin Sealant Kit (Yueling®, Hangzhou Puji Medical Technology Co. Ltd, Hangzhou, China) is composed of freeze-dried powder of fibrinogen and thrombin and of relevant solutions. Stored at 4 °C, the kit needs to reach room temperature. Then fibrinogen (Component I, > 30 mg/ml) is dissolved by sodium chloride solution (Activator I, 6.0 to 7.0 mg/ml), and thrombin (Component II, 450 to 850 IU/ml) is dissolved by calcium chloride solution (Activator II, 35.0 to 45.0 mg/ml).

When receiving glue sealing, the patients in the two treatment groups will have drainage cessation. Two main components of FG are placed separately in a double-syringe system with distal mixing catheter. When applied, equal amounts of fibrinogen and thrombin are mixed and the fibrin sealants are to form within 10 seconds. In order to assure total occlusion of the internal hole, the full length of the fistula tract must be determined by image examination prior to the procedure or with assistance of endoscopy [16].

The glue-sealing procedure could be repeated up to three times within the 14-day glue treatment period. A repeat sealing could be conducted if the fistula persists for 5 days after the first procedure. After the 14-day period, patients who fail to achieve medical closure are evaluated to further exclude possible factors disturbing healing, such as infection, foreign body, *etcetera.* These unhealed fistulas will either be treated by definitive surgery or continue to be treated conservatively based on the patient’s best interest and the physicians’ discretion.

Once glue sealing is applied, parenteral nutrition that provides calories of 20 to 25 kcal/kg is initiated through the peripheral vein or central venous catheter. Fistula drainage will be evaluated every day until the drainage decreases to zero, which is defined as fistula closure [17]. It also needs confirmation by contrast enhanced computed tomography at each follow-up visit to verify the complete closure of internal and external openings of the fistula tract. When the closure is achieved, a nasointestinal tube is to be placed and the enteral feeding (2,000 ml/d) is restarted gradually. Other SOC measures can be conducted when needed.

#### Outcomes

The primary outcome of the trial is fistula closure time (defined as the interval between the day of enrollment and day of fistula closure) during the 14-day treatment period. Fistula closure is defined as complete closure of the fistula tract and internal and external openings later, which will be confirmed by contrast enhanced computed tomography at each follow-up visit where there is no drainage or any sign of inflammation [17].

In addition to the primary outcome measure of fistula closure, secondary outcomes include closure rates up to 14 days, closure rates up to 180 days, fistula recurrence rates and the incidence of adverse events and severe adverse events up to 180 days (defined as an event that was fatal or life-threatening, led to additional hospitalization or disability or required an intervention to prevent one of these outcomes).

#### Participant timeline

All patients with ECFs in each study site receive SOC, and the fistula output will be evaluated every day. In case of daily output less than 200 ml, the inclusion criteria will be assessed, and imaging examination will be performed to exclude abscesses, obstruction, *etcetera.* Then participants are randomly allocated to Group A (autologous fibrin glue), Group B (commercial fibrin glue) or Group C (drainage cessation). Once enrolled and allocated to Group A, autologous PRFG needs to be prepared. The study period is set as 14 days after the day of enrollment, and fistula drainage will be evaluated every day. All patients are followed up for at least 180 days. The outpatient visits will be scheduled for 1 month, 3 months and 6 months after enrollment (Fig. 1).

**Fig. 1 Fig1:**
[figure not shown]
Study design. Patients are randomly allocated to group A (autologous fibrin glue), group B (commercial fibrin glue) or group C (drainage cessation). After glue application or drainage cessation, fistula drainage will be evaluated for 14 days, during which a maximum of three times of glue sealing will be conducted for patients in groups A and B. Both efficacy and safety outcomes will be assessed during the whole study period.

